#### Visit V1

During this visit (2 months after the randomization), stool will be collected using the OMNIgen®-GUT kit, blood drops deposited on blotting paper, data quality estimations made using the SF36 questionnaire, a survey of food ingestion frequency will be performed to describe dietary habits (SU-VI-MAX2 U557 Inserm) [20], a questionnaire investigating physical activity will be completed [21], and a urine pregnancy test realized. Patients will be randomly assigned a sample condition and scheduled to commence treatment the same day.

#### Follow-up visits

Six follow-up visits, interspersed at 6-month intervals, will be scheduled for the 4-year follow-up period: M6, M12, M18, M24, M30, and M36 (Table 2). During these visits, the patient will be provided with the next course of medication and compliance will be monitored. Medical examinations will be performed and additional colonoscopies scheduled as necessary. Urine pregnancy tests will be performed as described previously. Patients will be asked to report on any side-effects they had experienced as well as if they are undergoing other treatments, including self-medication. Further compliance and side-effect data will be collected, via telephone call, approximately 3 months before each follow-up visit.

**Table 2 Tab2:** Research timeline

	V0, inclusion	V1, M0	V2, M6	V3, M12	V4, M18	V5, M24	V6, M30	V7, M36	V8, M42	V9, M48
Protocol information	**X**									
Informed consent	**X**									
Antecedent	**X**									
Clinical exam	**X**		**X**	**X**	**X**	**X**	**X**	**X**	**X**	**X**
Blood analysis	**X**									
Chromo-colonoscopy	**X (< 6 months)**			**If necessary**		**X**	**If necessary**			**X**
Stool collection		**X**								**X**
Nutritional survey	**X**	**X**								
Physical activity survey	**X**	**X**								
Quality of life survey		**X**								**X**
Blood drops blotting paper		**X**								
Pregnancy test		**X**	**X**	**X**	**X**	**X**	**X**	**X**	**X**	**X**
Randomization		**X**								
Treatments dispensation		**X**	**X**	**X**						
Adverse effects			**X**	**X**	**X**	**X**	**X**	**X**	**X**	**X**
Compliance observation			**X**	**X**	**X**	**X**	**X**	**X**	**X**	**X**

#### End-of-study visit

Approximately 48 months after inclusion, a final colonoscopy with chromoendoscopy will be performed, as in previous visits, medical examinations and blood analyses performed. Quality of life will be assessed on the SF36 questionnaire. An exclusion period will restrict patient enrollment in another trial for the 3-month period succeeding the trial. A summary table of the study timeline is available in Table 2.

### Biological collections

Biopsies will be performed for each patient. Tissue samples and smears will be prepared from samples taken during colonoscopies and then sent by post to the coordination centers for storage. Stool samples (prepared at home using an OMNIgen®-GUT kit) will be taken at the beginning and end of the treatment period. Samples will be labeled with an inclusion number and issue date then securely posted to a diagnostic/storage center. Blood samples will be collected on a blotting paper from which DNA will be subsequently extracted.

### Recruitment

Patients will be recruited from 34 French specialist institutes with dedicated oncogenetic teams managing Lynch patients. Almost 3000 patients are registered with these centers. All patients are tested for gene alterations and MMR deletions and are monitored closely. The HNPCC-Lynch Patient Association will assist in the recruitment of patients to this study by notifying its subscribers about the study’s existence.

### Statistical methods

The initial characteristics of the population will be described globally and by group (age, sex, BMI, MSI–MLH1; MSH2; MSH6; PMS2–). The continuous variables will be described using average, standard deviation, median, minimum, and maximum. The qualitative variables will be described using frequency and percentages.

The main analysis will be done in intention of treat. A per-protocol analysis will also be performed. The statistical significance level will be 5% and all tests will be bilateral.

The main end-point analysis will be performed using logistic regression with age (< and ≥ 45 years) and using center adjustment. A specific analysis of the dose effect will be performed between the two arms of aspirin (100 mg vs 300 mg) in the case of an overall effect in the aspirin group. A subgroup analysis will be performed according to age and the *p* value was corrected according to the Bonferroni method. A center effect analysis effect will also be performed when institutes provided a small number of patients. An intermediate analysis will be carried out after 24 months of treatment on secondary judgment criteria. The Kaplan-Meier method and a log-rank test will be used to assess the effect of treatment on the delay of the appearance of the first adenoma. Patients who presented an adenoma during follow-up according to MMR status, colon cancers diagnosed, and post-colonoscopy colon cancers will be evaluated by logistic regression with age and center adjustment. Sessile serrated adenoma and adenomatous burden will be evaluated using a Poisson or a binomial regression approach.

All of the patients included in the study will be considered in the analysis. For the main analysis, lost subjects will be considered failures, regardless of the treatment group. Sensitivity analyses will also be performed, using multiple imputation methods.

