## Introduction

Lynch syndrome is the most common cause of inherited colorectal cancer. It is linked to germline alterations in mismatch repair genes that confer a high lifetime risk of colorectal cancer estimated to be as high as 60%. Most colorectal cancers arise from asymptomatic adenomas. Early detection and removal of adenomas can prevent their transformation into cancers. Colonoscopy is recommended every 2 years in Lynch syndrome patients above the 20–25-year-old age bracket, and every year when colonic neoplasia has been detected [1]. Efficient chemoprevention has the potential to represent a cost-effective intervention in these high-risk patients and could allow a delay in colonoscopy surveillance. Aspirin therapy decreases the risk of colorectal cancer in experimental models. Multiple mechanisms have been reported to explain this effect [2]. Several epidemiological studies have shown that the regular use of low dose aspirin (75 to 300 mg/d) is associated with a 20 to 30% reduction in the risk of sporadic colonic adenomas and colorectal cancer regardless of family risk [3]. Seven randomized controlled trials (RCT) evaluating adenoma recurrence are available [4–10]. Five out of seven trials showed a significant decrease in neoplasia recurrence [4–6, 8, 10]. A meta-analysis of four of these studies confirmed a decrease in colorectal adenoma recurrence [11]. In a pooled analysis of cardio-vascular prevention RCTs, and in a meta-analysis, daily aspirin was associated with a reduced risk of CRC and CRC associated mortality [12]. However, in two large, recent, randomized trials in diabetic patients and in healthy elderly patients, aspirin use showed no protection for colorectal cancer [13, 14]. The Colorectal Adenoma/carcinoma Prevention Programme 2 (CAPP-2) evaluated aspirin 600-mg (300 mg b.i.d) effect in LS patients. The primary analysis of this prospective randomized trial showed no significant decrease in CCR risk in LS patients under daily aspirin [15]. However, a preplanned secondary analysis after an extended follow-up (mean 56 months) showed a significantly reduced risk of CRC in the aspirin group in the per-protocol analysis [16]. In this study, the endoscopic follow-up was sub-optimal with a relatively low detection rate of colorectal neoplasia compared to the actual reported rate [17], or the chromo-endoscopy derived rate [18]. The exact effects and clinical benefits of aspirin therapy are still to be consolidated in LS patients. Notably, aspirin’s preventive benefits are expected to outweigh its putative adverse effects in these high-risk patients.

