
### Intervention

A centralized randomization with stratification by age (< or ≥ 45 years) and center will be performed. It was not possible to obtain the 2 doses of aspirin (100 and 300 mg) with the same aspect; therefore, 2 different types of placebo tablets were used: one similar to the 100-mg aspirin tablet and the other similar to 300-mg tablet. Patients and investigators could identify the size of the tablet without knowing the assignment arm (aspirin or placebo). Patients are randomized to one of the four treatment conditions: aspirin 100 mg, aspirin 300 mg, placebo of aspirin 100 mg, and placebo of aspirin 300 mg, according to a ratio 1: 1: 1: 1 using a previously established randomization standardized protocol. A total blind would have required the daily intake of 2 different tablets (1 active and 1 placebo or 2 placebos). This choice was made to favor compliance by reducing the number of tablets prescribed. Patients and investigators can therefore identify the size of the tablet but without knowing the assignment arm (aspirin or placebo) (protocol version 3.0 dated 2 June 2017).

Circumstances under which unblinding is permissible are severe digestive hemorrhage, traffic accident, and another situation requiring knowing if the patient is on aspirin. The procedure for revealing a participant’s allocated intervention during the trial consists in calling the project manager or, in case of emergency, the poison control center at Fernand Widal Hospital.

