### Secondary end-points

The secondary end-points are defined as the adenomatous polyp burden (calculated as the sum of adenomatous polyps diameters as measured during planned surveillance colonoscopies); the delay between the inclusion and the first observed adenoma; the number of patients who presented with an adenoma during the follow-up according to the affected gene (MLH1, MSH2, MSH6, PMS2, other or no abnormality identified); the number of patients with sessile serrated adenoma, colon cancers diagnosed, and post-colonoscopy colon cancer (diagnosed between two planned surveillance colonoscopies); and time of apparition.

The quality of bowel cleansing, the number of chromo-colonoscopies performed in follow-up sessions, the number of remaining tablets in blisters, and side effects are reported.

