### Participant timeline

#### Screening visit

The selection period takes place up to 180 days before the inclusion visit. The investigator collects the patient’s personal history: characteristics of LS, genetic test results, and colonoscopy results. During this screening visit, the informed consent is given with the information notice.

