#### Visit V0

The investigator first will obtain written consent from all patients. Inclusion and exclusion criteria will be checked. The first colonoscopy will be performed no longer than 180 days before the inclusion visit to assess pre-existing lesions. Colonoscopies will be performed according to INCa (Institut National du Cancer) recommendations. Colonoscopies may be performed outside the investigator’s hospital, including any public or private institutions. All identified polyps will be removed during colonoscopies prior to the inclusion visit. During each colonoscopy, patients are scored against quality criteria as defined by the Digestive Endoscopic French Society (SFED) guidelines [19]: adequately prepared bowel (Boston ≥ 7), cecal intubation rate ≥ 90% (complete visualization of the cecum and appendicular tripod, endoscope terminal located in the proximity of the appendiceal orifice confirmed by a photo or a video), appropriate polypectomy technique (biopsy forceps removal for polyps ≤ 3 mm in size and snare polypectomy for larger polyps), and withdrawal time ≥ 6 min. Adenomatous, sessile serrated adenoma and polyp burden will also be collected.

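### The primary logistic model leaves out two plausible baseline predictors that are already collected, adenoma at the clearing colonoscopy and affected MMR gene; adding them could gain about 0 to 4 points of power

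*Protocol article*

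**What the plan says.** The Protocol article, Statistical methods, names the covariates of the primary model: "The main end-point analysis will be performed using logistic regression with age (< and ≥ 45 years) and using center adjustment". They match the randomisation strata in the Intervention section: "A centralized randomization with stratification by age (< or ≥ 45 years) and center will be performed".

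Two other baseline variables are recorded but not used in that model.

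- **Adenoma findings at the clearing colonoscopy.** The investigator records "characteristics of LS, genetic test results, and colonoscopy results" at screening. Under Visit V0 the article adds: "Adenomatous, sessile serrated adenoma and polyp burden will also be collected".
- **Affected MMR gene.** The Recruitment section states: "All patients are tested for gene alterations and MMR deletions and are monitored closely". Gene appears in the baseline description ("The initial characteristics of the population will be described globally and by group (age, sex, BMI", a list that goes on to the four genes) and in a secondary endpoint, "the number of patients who presented with an adenoma during the follow-up according to the affected gene (MLH1, MSH2, MSH6, PMS2, other or no abnormality".

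The Sample size section assumes 30% with an adenoma on placebo, a 28% reduction on aspirin, 5% alpha and 80% power, giving 426 per pooled group. It assumes no gain from covariates.

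**The concern.** The trial enrols patients both with and without an adenoma at the clearing colonoscopy, and carriers of different genes, and then asks who has an adenoma during follow-up. The article gives indirect reasons to expect both variables to predict that outcome. The Introduction says that surveillance is "every year when colonic neoplasia has been detected" instead of two-yearly, and the outcome is to be reported by affected gene.

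Adjusting a logistic model for baseline variables that predict the outcome raises the power of the treatment test. It also corrects chance imbalance in those variables, for which the randomisation does not stratify. At stake is a modest amount of power in a trial sized at 80%, for a change that needs no new data. The terms must be named before unblinding, because terms added later would look data-driven.

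**Working it through.** **1. The plan's own figure.** The inputs are from the Sample size section; tests are two-sided (Statistical methods).

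p1 = 0.30; p2 = 0.30 × (1 − 0.28) = 0.216; difference 0.084; mean 0.258; marginal odds ratio (0.216/0.784)/(0.30/0.70) = 0.643.

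n = [1.960 × √(2 × 0.258 × 0.742) + 0.842 × √(0.30 × 0.70 + 0.216 × 0.784)]² / 0.084² = (1.213 + 0.518)² / 0.007056 ≈ 425 per group.

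With the pooled variance throughout, n = 426. Power at 426 per group is 80.1%. The stated size is reproduced and needs no covariates to reach its target.

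**2. Gain from the two covariates.** The article gives no odds ratio, R² or prevalence for either variable, so these inputs are assumed: 30% with a baseline adenoma; four gene categories in shares of 35/40/17/8%; gene odds ratios 1/1.3/0.7/0.5 where a gene effect is present. The simulation had 852 patients and 4,000 runs per scenario. Marginal rates were held at 30% and 21.6%, with a Wald test at 5%. Age and centre were not simulated. R² is the variance of the predicted placebo risk divided by 0.30 × 0.70 = 0.21.

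| Assumed effects | R² | Power without (%) | Power with (%) | Gain (points) |
|---|---|---|---|---|
| None | 0 | 80.1 | 80.1 | 0 |
| Baseline adenoma OR 1.5 only | 0.008 | 80.5 | 80.6 | 0.1 |
| Gene only | 0.016 | 80.3 | 81.0 | 0.7 |
| OR 1.5 + gene | 0.023 | 79.8 | 80.7 | 0.9 |
| OR 2 + gene | 0.038 | 80.7 | 82.1 | 1.4 |
| OR 3 + gene | 0.071 | 79.5 | 82.2 | 2.7 |
| OR 4 + gene | 0.104 | 80.0 | 84.3 | 4.3 |

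Monte Carlo error is about √(0.8 × 0.2/4000) = 0.6 points per power figure.

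**3. Cross-check by approximation.** With effective size N/(1 − R²), R² of 0.02, 0.05 and 0.10 gives power of 80.9%, 82.1% and 84.1%. Equivalently, 426 × (1 − R²) = 418, 405 and 384 per group would keep the planned power. This agrees with the table.

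**4. With centre terms in both models.** Two further simulations with 34 centres used 1,500 runs per scenario. Only the differences within each pair should be read.

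- With age and centre in both models: no association 82.5 to 82.7%; OR 2 plus gene 82.8 to 84.1%; OR 3 plus gene 81.0 to 84.7%; OR 4 plus gene 81.7 to 84.1% (error about 1 point per figure). Type I error of the fuller model was 5.3% (OR 3) and 5.9% (no association, the same as for the planned model).
- With centre SD 0.4 on the logit scale and blocks of 4: gains of 0.4, 1.3 and 4.3 points at baseline odds ratios of 1.5, 2.5 and 4 with gene effects (paired standard errors 0.5 to 0.7). The first cannot be told from zero.

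**5. Costs.** For the same marginal effect, the conditional odds ratio moves from 0.643 to between about 0.61 and 0.64. One adenoma term and up to four gene terms (five categories) would join a model that may already carry 33 centre terms, with about 0.258 × 852 = 220 expected events.

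**6. Losses.** Statistical methods counts lost patients as failures. With an assumed loss L, equal in both groups, each rate becomes L + (1 − L)p. At L = 10% the rates are 37.0% and 29.4%, and unadjusted power falls to 64.9%; at L = 5% it is 72.4%. In a simulation with 10% loss and OR 3 plus gene, the added covariates moved power only from 68.3% to 69.1%. A second gave gains of 0.7, 1.2 and 3.4 points at odds ratios of 1.5, 2.5 and 4.

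**The case against.** The strongest reply is that nothing here is wrong. The model is prespecified, adjusts for exactly the stratification factors, and delivers the power that was promised. Randomisation already makes the test valid, and supportive adjusted analyses may sit in an analysis plan that is not shown. Most of this stands: the planned model is not an error. It does not dispose of the point, because the article itself names the primary model's covariates, and the suggestion concerns that stated choice.

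The second reply is that prognostic strength is assumed. This stands in full. A surveillance recommendation after neoplasia is not an estimate of adenoma risk, and reporting an endpoint by gene does not show that gene predicts it. The 30% share with a baseline adenoma also has no source in the article. Table 1 asks for an indication for two-yearly surveillance while the Introduction gives yearly surveillance after neoplasia, so the share could be lower, and the gain with it.

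A reader might infer that the plan throws away power worth 8 to 11% more patients. Simulations that assume a baseline-adenoma odds ratio of 2.5 with a lower-risk-gene odds ratio of 0.5, or 4 with 0.33, do give 79.6 to 82.7% and 82.0 to 85.8%. The equivalent size ratios are ((1.96 + z₂)/(1.96 + z₁))² = 1.08 and 1.11. Those are favourable cases only; weak or null effects bring the gain close to zero, and the document cannot rule them out.

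**Conclusion.** The point holds as an efficiency improvement. The primary model omits two baseline variables that are collected before treatment and are plausibly prognostic. Including them would be expected to raise power by about 0 to 4 points, about 1 to 3 for moderate strength (baseline-adenoma odds ratio 1.5 to 3 plus gene effects). No loss of power was seen when the covariates carried no information. All of this rests on assumed prevalences and odds ratios.

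Two stronger readings are not supported. The gain is not entirely free, since the odds ratio becomes conditional on more covariates and a few parameters are added; these costs are small. Nor does the change rescue a trial short of reserve: the power lost by scoring lost patients as failures is a separate and larger matter, and these covariates recover little of it.

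**What to change.** Before unblinding, extend the primary logistic model to treatment, age group, centre, adenoma at the baseline clearing colonoscopy (yes/no) and affected gene (MLH1, MSH2, MSH6, PMS2, other or none identified). Fix in advance the rule by which sparse gene categories are collapsed. Use the same terms in the multiple-imputation model of the sensitivity analysis. Keep the age-and-centre model as a sensitivity analysis, and state that the primary odds ratio is conditional on the added covariates.

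The cost is a change of analysis wording. The article already provides for collecting both variables before treatment, and the sample size need not change.

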### Sample size

The main objective of this trial is to show that adenoma prevalence is less important in the aspirin group (regardless of the dose) than in the placebo group. The initial hypothesis was constructed with a 30% adenoma prevalence in the placebo group and a reduction of 28% expected in the aspirin group, based on our previous RCT on patients without Lynch syndrome but with a history of colorectal adenomas [8]. For a 5% alpha risk and 80% power, according to this hypothesis, 426 patients will be needed in the aspirin group (213 patients for aspirin 100 mg arm and 213 patients for aspirin 300 mg arm) and 426 patients in the placebo group (213 patients for placebo aspirin 100 mg arm and 213 patients for placebo aspirin arm 300 mg). A total of 852 patients will be included.

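### The age subgroup analysis rests on Bonferroni-corrected p values with no treatment-by-age interaction test named, so it cannot show whether aspirin's effect differs by age

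*Protocol article*

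**What the plan says.** The protocol article deals with age subgroups in one sentence under Statistical methods: "A subgroup analysis will be performed according to age", with the p "value was corrected according to the Bonferroni method". The same section sets the general rule: "The statistical significance level will be 5% and all tests will be bilateral".

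Age has two classes, under 45 and 45 or over. It is a stratification factor at randomization (Intervention) and an adjustment covariate in the logistic model for the main end-point (Statistical methods). No product term between treatment and age is mentioned anywhere in the article, and the number of tests covered by the Bonferroni correction is not given.

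**The concern.** With a single two-level factor, the question of whether aspirin's effect differs by age is answered by one interaction test, and one test needs no Bonferroni correction. The correction therefore points to several p values, most naturally one aspirin versus placebo comparison in each age class, each judged at 0.05/2 = 0.025.

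Such tests ask whether there is an effect in this class, then in that one. They do not compare the classes. Each class holds only part of a sample that was sized for 80% power overall, so one class can easily reach significance and the other miss it when the true effect is identical. Lowering the threshold leaves the question unanswered.

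At stake is a report that seems to show benefit in one age class only, when the data are what a uniform effect would produce. The Discussion makes such a reading attractive: it speculates that aspirin's action depends on when exposure occurs, and connects this with disappointing results in older people.

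**Working it through.** **Inputs from the article**
- Rates (Sample size): "30% adenoma prevalence in the placebo group and a reduction of 28% expected in the aspirin group". The 28% is a relative reduction: 0.30 × 0.72 = 0.216, a difference of 0.084.
- Size and error rates (Sample size): "For a 5% alpha risk and 80% power, according to this hypothesis, 426 patients will be needed in the aspirin group", and "A total of 852 patients will be included".
- Allocation (Intervention): "according to a ratio 1: 1: 1: 1", hence 1:1 for pooled aspirin against pooled placebo.

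**Assumptions**
- The age split is not stated; 50/50, 40/60 and 30/70 are used.
- The Bonferroni level is 0.05/2 = 0.025 per class.
- The true effect is 30% versus 21.6% in both classes.
- Center adjustment is not modelled.

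**Step 1. The plan's own figure.** With mean rate 0.258, √(2 × 0.258 × 0.742) = 0.6188 and √(0.30 × 0.70 + 0.216 × 0.784) = 0.6159:

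n = (1.96 × 0.6188 + 0.8416 × 0.6159)² / 0.084² = 424.7, so 425 per group. The article states 426. Power at 426 is 80.1%. The figure is reproduced.

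**Step 2. Power within one age class.** For n per treatment group in the class:

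power = Φ[(0.084√n − z × 0.6188) / 0.6159], with z = 2.2414 at two-sided 0.025.

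For a 50/50 split, n = 213: (1.2259 − 1.3870) / 0.6159 = −0.261, so power is 39.7%.

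**Step 3. Chance that exactly one class is significant.** The classes are independent. With powers A and B, it is A(1 − B) + B(1 − A). For 50/50: 2 × 0.397 × 0.603 = 0.479.

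| Age split | Power, smaller / larger class (0.025) | Exactly one | Both | Neither | Exactly one at 0.05 per class |
|---|---|---|---|---|---|
| 50/50 | 39.7% / 39.7% | 47.9% | 15.8% | 36.4% | 50.0% |
| 40/60 | 31.9% / 47.2% | 49.0% | 15.0% | 36.0% | 51.3% |
| 30/70 | 23.9% / 54.1% | 52.1% | 12.9% | 34.9% | 55.0% |

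Simulation of 400,000 trials per split gives the same picture (47.8%, 49.1% and 52.2% for exactly one at 0.025). Among simulated trials with a significant overall result (80%), 57%, 59% and 63% show exactly one significant class.

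**Step 4. What Bonferroni does control.** With no effect in either class (30% in all groups, 50/50), the simulated chance of any significant class is about 5% with the correction (4.9% one class, 0.1% both) and about 10% without it (9.5% and 0.3%). That is a different error from declaring an age difference that does not exist.

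**Step 5. The interaction test.** Under the uniform effect, a Wald test on the difference in log odds ratios at two-sided 5% falsely declares an age difference in 4.8% to 5.0% of simulated trials across the three splits.

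Its power is low. Suppose 30% versus 21.6% in one class and 30% versus 30% in the other, split 50/50:
- Log odds ratio in the first class: ln[(0.216 × 0.70) / (0.784 × 0.30)] = −0.442.
- Variances: 1/(213 × 0.21) + 1/(213 × 0.1693) = 0.0501, and 2/(213 × 0.21) = 0.0447.
- Standard error: √0.0948 = 0.308. Ratio: 0.442/0.308 = 1.435. Power: about 30%.

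With the effect confined to the smaller class, power is about 29% at 40/60 and 26% at 30/70.

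**The case against.** The strongest reply is that testing each age class at 0.025 is a valid answer to a different question, namely whether aspirin works in that class. Step 4 supports this: the correction keeps the chance of any false positive at about 5%. The article does not say that effect modification will be inferred by comparing p values, so the 48–52% becomes a rate of wrong claims only if discordant results are read that way. This stands, and the figure should be presented as the frequency of discordant results under a uniform effect. Even for the narrower aim, though, power of 24% to 54% per class makes non-significance in a class close to uninformative.

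A second reply is that the article condenses a longer protocol, and an analysis plan that is not shown may add an interaction test. A reader might infer that such a test has been ruled out; the article does not say so. The point does not rest on that omission. The article does fix a subgroup method, and that method cannot show whether the effect differs by age.

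Two further inferences are not supported:
- That Bonferroni makes discordant results more common. It lowers them slightly, for example from 50.0% to 47.9% at a 50/50 split.
- That the secondary end-point by affected gene has the same fault. For it, Statistical methods gives logistic regression with age and center adjustment, with no Bonferroni correction and no separate test within each gene.

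**Conclusion.** The point holds in a limited form. The planned age subgroup analysis, read naturally as two within-class tests at 0.025, does not address whether aspirin's effect differs by age. Under the same effect in both classes, about half of all trials (48% to 52%) would show significance in exactly one class, against about 5% in which an interaction test would falsely declare a difference.

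This rests on the article's planning rates, on assumed age splits and on two tests being the ones corrected. The conclusion is the same across the splits. It also survives unequal placebo rates: with 20% and 40% in equal classes and the same relative reduction, exactly one class is significant in 54% of simulated trials.

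The matter is worth correcting but confined to a subgroup analysis. The sample size and the main end-point analysis are untouched.

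**What to change.** Replace the subgroup sentence under Statistical methods. Suggested content: the treatment-by-age-group term (under 45 versus 45 or over) will be tested once, at two-sided 5%, in the logistic model for the main end-point with its age and center adjustment; odds ratios for aspirin versus placebo will be given for each age class with 95% confidence intervals, and significance will not be claimed within a class. The Bonferroni clause then falls away. If a fuller protocol or analysis plan already contains this test, aligning the wording is enough.

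The change is one sentence, with no effect on sample size, randomization or data collection. It has two costs. No claim of significance within an age class is possible. And with about 25–30% power when aspirin works in one class only, a non-significant interaction must not be reported as proof of a uniform effect; the text should say so.

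### Age group and centre stratify randomisation and enter the logistic models, but neither is named for the log-rank test or the Poisson/binomial regressions; if they are left out, some secondary tests are conservative

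*Protocol article*

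**What the plan says.** On allocation, the protocol article (Intervention) states: "A centralized randomization with stratification by age (< or ≥ 45 years) and center will be performed". The four arms are allocated "according to a ratio 1: 1: 1: 1 using a previously established randomization standardized protocol", so pooled aspirin against pooled placebo is 1:1. On sites (Recruitment): "Patients will be recruited from 34 French specialist institutes".

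Statistical methods then assigns an analysis to each endpoint:

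- Primary endpoint: "The main end-point analysis will be performed using logistic regression with age (< and ≥ 45 years) and using center adjustment".
- Time to first adenoma: "The Kaplan-Meier method and a log-rank test will be used to assess the effect of treatment on the delay" until the first adenoma. No strata are named.
- Adenoma by mismatch-repair status, colon cancers and post-colonoscopy cancers: logistic regression, again with age and centre adjustment.
- Serrated lesions and burden: "Sessile serrated adenoma and adenomatous burden will be evaluated using a Poisson or a binomial regression approach". No covariates are named.

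The last three items stand in consecutive sentences. The test level is common to all: "The statistical significance level will be 5% and all tests will be bilateral".

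**The concern.** Stratified randomisation balances age group and centre between the arms, so differences between strata contribute little to the treatment contrast. An analysis that ignores the strata can still count those differences as random error. Its standard error is then too large, its true type I error falls below the nominal 5%, and it gives up power that the design has already paid for.

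The article respects the randomisation factors in the logistic models. It does not name them for the log-rank test or for the burden and serrated-lesion models, and gives no reason for the difference. At stake is some sensitivity on time to first adenoma and, depending on the model chosen, on the serrated-lesion and burden comparisons. Statistical methods also places the 24-month intermediate analysis on secondary criteria, so some of these results may be read before the primary one.

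**Working it through.** **1. The plan's own figure.** Sample size gives 30% on placebo and a 28% relative reduction, so 0.30 × 0.72 = 21.6% on aspirin. With two-sided 5% and 80% power, the mean proportion is 0.258 and

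n = [1.960·√(2·0.258·0.742) + 0.842·√(0.30·0.70 + 0.216·0.784)]² / 0.084² = 425 per group,

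against 426 stated. Power at 426 per group is 80.1%. The planning figures reproduce and are used below. The article gives no power for the secondary tests.

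**2. Size of the effect, age only.** The article gives no age-specific risks, so these are assumed, averaging 30% with half the patients in each age group. For a comparison of proportions with exact balance, the true variance is proportional to the mean of p(1−p) within strata, while the unstratified test uses 0.30 × 0.70 = 0.21. Type I error is 2[1 − Φ(1.96/√ratio)]. Beside it are simulated log-rank results (852 patients, 4,000 runs, relative risk 0.72 for power).

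| Risk <45 / ≥45 | Within-stratum mean p(1−p) | Ratio to 0.21 | Type I error, formula | Type I error, log-rank, unstratified → age-stratified | Power, same order |
|---|---|---|---|---|---|
| 20% / 40% | (0.16+0.24)/2 = 0.200 | 0.952 | 4.5% | 4.5% → 4.9% | 79.9% → 81.4% |
| 15% / 45% | (0.1275+0.2475)/2 = 0.1875 | 0.893 | 3.8% | 4.0% → 5.1% | 80.8% → 83.4% |
| 10% / 50% | (0.09+0.25)/2 = 0.170 | 0.810 | 2.9% | 3.0% → 5.3% | 81.3% → 85.6% |

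Formula and simulation agree. The power differences are 1.5, 2.6 and 4.3 points.

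**3. Age and centre together.** There are 34 × 2 = 68 possible strata, or 852/68 ≈ 12.5 patients each. A second simulation used 34 centres of unequal size, permuted blocks of four within centre and age group, and first adenoma seen at 24 or 48 months. The hazard ratio was ln(0.784)/ln(0.70) = 0.68. There were 6,000 runs under the null and 3,000 under the alternative. Block size, centre sizes and strata strength are assumptions. Compare within rows only, because the overall event rate is not held exactly fixed across rows.

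| Age hazard ratio, SD of log centre effect | Type I error: unstratified / age strata / age × centre strata | Power, same order |
|---|---|---|
| 1.0, 0 (none) | 5.2 / 5.3 / 5.4% | 82.0 / 82.1 / 81.0% |
| 1.5, 0.2 (weak) | 4.6 / 4.7 / 4.9% | 79.0 / 79.3 / 79.3% |
| 2, 0.3 (moderate) | 4.7 / 5.0 / 5.5% | 77.2 / 77.6 / 77.5% |
| 3, 0.5 (strong) | 3.6 / 4.2 / 4.7% | 73.2 / 75.4 / 77.6% |
| 4, 0.8 (very strong) | 2.5 / 3.2 / 5.0% | 62.5 / 65.6 / 71.3% |

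The standard error is about 0.3 points on type I error and 0.7–0.9 points on power. The unstratified loss against full stratification is 0.3 points in the weak and moderate rows, 4.4 in the strong row and about 9 in the very strong row. With no prognostic strata, full stratification costs 82.0 − 81.0 = 1.0 point.

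**4. The Poisson and binomial models.** A binomial test follows the formula in step 2. A model-based Poisson test does not. Its variance equals the mean, so between-stratum spread never enters it. In the same simulations its type I error was 4.9–5.8%. If patients vary beyond their strata, the true variance exceeds the mean. With a mean count of 0.5 and gamma frailty of variance 1, the ratio is (0.5 + 0.25)/0.5 = 1.5, and 2[1 − Φ(1.96/√1.5)] = 11%. The simulated range was 10–19%. A test whose variance reflects the total spread gave 4.5%, 4.4%, 3.6% and 2.9% from weak to very strong strata.

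**The case against.** The strongest reply is that this is an inference from silence. The article never says these analyses will be unadjusted. It leaves even the regression family open for burden, so it is plainly a summary, and covariates for secondary models are often left to the full protocol or analysis plan. A reader might infer that the trial has decided to ignore its stratification factors; the text does not establish that. What remains is the contrast. Where adjustment was meant, the article says so twice, once in the sentence between the two that omit it, and a log-rank test named without qualification is ordinarily the unstratified one.

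The second reply is that the effect is small, concerns secondary endpoints only and, for the log-rank test, errs towards caution, so it creates no false positive. That stands. With weak to moderate strata in step 3 the power difference is within simulation error, and clear losses need roughly threefold or larger differences between age groups, or strong centre effects as well.

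Two further inferences are tempting. One is that a secondary result could contradict the primary one merely because the adjustment differs; these are different endpoints, and nothing in the article shows it. The other is that the hazard ratio will be diluted; the article names no hazard ratio.

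**Conclusion.** The point holds in a limited and conditional form. The randomisation factors are treated unevenly across the endpoints of one trial. If the text is followed literally, the log-rank test is conservative to the extent that age or centre is prognostic: type I error about 4.5–4.7% and 0–1.5 points of power for weak to moderate strata, about 2.5–4% and 3–9 points for strong to very strong ones. These ranges rest on assumed strata strengths, an assumed block size and complete follow-up. The same direction applies to an unadjusted binomial or overdispersion-robust model.

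A reader might extend this to all the secondary tests and conclude that each runs below 5%. That is not supported. A model-based Poisson test stays near 5%, and any excess above it comes from overdispersion, which is a separate matter from missing adjustment. The primary analysis is adjusted for both factors and is not affected. This is a modest improvement worth making because it is nearly free.

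**What to change.** In Statistical methods:

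- Specify a log-rank test stratified by age group (<45/≥45), with centre handled either as an added stratum or through a Cox model that includes both factors. Fix the choice before unblinding. Age strata alone recover only part of the loss when centre matters: in the strong row, power goes from 73.2% to 75.4%, against 77.6% with both factors.
- Add age group and centre to the Poisson or binomial models for serrated lesions and adenoma burden, as the logistic models already do.

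If the full protocol or analysis plan already says this, aligning the article's wording is enough. The cost is wording only. Both factors are already recorded for randomisation, and no patient or visit is affected. If neither factor turns out to be prognostic, full age-by-centre stratification costs about 1 point of power (81.0% against 82.0%).
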